# Study protocol: biomechanical testing, finite element analysis and prospective, randomized, clinical study of single screw cephalomedullary nailing versus integrated dual interlocking screw fixation for unstable (31A2_1–3_) intertrochanteric fractures in patients > 70 years old

**DOI:** 10.1186/s13018-023-04009-8

**Published:** 2023-07-28

**Keywords:** Intertrochanteric fractures, Biomechanical testing, Finite element analysis, Single cephalomedullary nailing, Integrated dual interlocking screw nailing

## Abstract

**Background:**

Hip fractures are an increasingly common consequence of falls in older people that are associated with a high risk of death and reduced function. The vast majority of intertrochanteric fractures require surgical treatment to withstand early mobilization and weight bearing, which prevents complications due to prolonged bed rest and aids in fracture healing.

**Methods:**

This study is compromised by two parts, the experimental study and the clinical part. In the first part, a standard 130° nail will be used with the appropriate lag screw(s) and dynamic distal locking in synthetic osteoporotic femurs and the transmission of forces in the proximal femur, measured by a cortical surface-strain distribution, will be evaluated using digital image correlation. Finite element parametric models of the bone, the nails and their interface will be also developed. Finite element computations of surface strains in implanted femurs, after being validated against biomechanical testing measurements, will be used to assist the comparison of the nails by deriving important data on the developed stress and strain fields, which cannot be measured through biomechanical testing. In the other part, will set up a prospective, randomized, comparative clinical study among the Gamma3 and IT cephalomedullary nailing, in order to investigate if there are any statistical important differences in the main radiological measurements and functional status in closed unstable intertrochanteric fractures (A21-3) in patients aged over 70 years old at the 24-week follow-up evaluation using patient reported disease-specific outcomes.

**Discussion:**

This study will be the first to compare clinical, radiological and biomechanical measurements of the two different cephalomedullary nails. Our main hypothesis is that the IT nail would provide better radiological outcome and probably better clinical results than the Gama3 nail.

*Clinical trial registration* International Standard Randomized Controlled Trial Number (ISRCTN): https://doi.org/10.1186/ISRCTN15588442, registered on 19/4/2022.

## Introduction

Hip fractures are an increasingly common consequence of falls in older people that are associated with a high risk of death and reduced function [1, 2]. In fact, hip fractures constitute one of the most common impairments worldwide in terms of loss in disability-adjusted years for people older than 60 years old [1, 3]. The absolute number of hip fracture hospitalizations in the US are estimated to approach 289,000 in 2030 with an expected increase to 4.5 million by the year 2050 [4, 5]. In the UK, there is an ongoing age-standardized fall of hip fractures of 0.5% per year, but it is estimated that the annual incidence will double in the next 25 years [6]. The consequences for hip fractures in elderly individuals are significant in terms of lives lost and the associated negative impacts on hip fracture patients’ functioning and quality of life [7, 8]. In a recent critical review of 38 studies by Dyer et al. [1], hip fracture survivors experienced significantly worse mobility, independence in function, health, quality of life and higher rates of institutionalization than age matched controls. Even with integrated, multidisciplinary models for the treatment of hip fragility fractures the in-hospital mortality rate was 2.4%, and the overall mortality at 1 year from the intervention 18.7%; full mobility status or a low impairment of mobility was reached 32.1% of patients [9]. The reported mortality rate at 1 year in a very recent study from the Swedish Hip Fracture Registry [10] was approximately 20% for women and 30% for men in a total population study of 289,603 first hip fractures during a 20-year-old period (1998–2017).

The vast majority of intertrochanteric fractures require surgical treatment to withstand early mobilization and weight bearing, which prevents complications due to prolonged bed rest and aids in fracture healing. The type of surgery is generally based on fracture pattern and patient characteristics and is usually carried out with Dynamic Hip Screw (DHS) devices or cephalomedullary nails (Proximal femoral nails [PFN], PFN-antirotation nails [PFNA], Gamma nails [GN], Trigen Intertan [IT] nails or other implants) [11–16]. The optimal device for surgical fixation of trochanteric fractures remains under debate [17–33]. Considering the substantial burdens attributed to the management of intertrochanteric fractures, we believe that more evidence is required to evaluate the effectiveness of a single lag cephalomedullary screw vs dual integrated screw nailing for unstable intertrochanteric fractures. The aims of the present study are:to perform a biomechanical testing between IT and Gamma3 in relation to axial stiffness, torsional stiffness, and failure load in unstable intertrochanteric fractures created in 4th-generation osteoporotic sawbones;to create finite element parametric models of the bone, the nails and their interface; finite element predictions of surface strains in implanted femurs, after being validated against biomechanical testing measurements, will be used to assist the comparison of the nails by deriving important data on the developed stress and strain fields, which cannot be measured through biomechanical testing. Such parameters including non-central lag screw(s) position in either the anteroposterior or lateral plane and varus or valgus reduction.To compare the clinical and radiological results of the two implants in a prospective, randomized clinical study in patients over 70 years old with unstable AO/OTA A2 fractures with a minimum follow-up of 6 months.

## Materials and methods

### Biomechanical study

#### Implants

The experimental work will be undertaken in the Laboratory of Technology and Strength of Materials at the Department of Mechanical Engineering and Aeronautics of Patras University. Two implant systems will be compared against biomechanical testing, the classic Gamma3 and the InterTan nail (IT).

The Gamma3®nail (Stryker, Mahwah, NJ, USA) that would be used in the current study has a length of 180 mm, 11 mm nail diameter and 130° neck-shaft angle and utilizes a single lag screw with a standard diameter of 10.5 mm. The Trigen Intertan (Smith + Nephew, Watford, UK) nail is a current generation IM device, featuring a dual lag screw configuration comprised of a 11.0 mm superior lag screw and a 7.0 mm smaller integrated screw that allows for linear compression of the fragments at the fracture site while providing high rotational stability [32, 33]. The proximal part of the nail has a trapezoid design that provides a pressfit fixation in the metaphyseal region thus positioning more material on the lateral side of the nail where tensile/stretching forces tend to be greatest. Finally, the “clothes pin” distal tip provides less rigidity to decrease the stress riser and reduce the incidence of anterior thigh pain. An 11 mm nail with a 130° neck-shaft angle will be used for the present study.

We would hypothesize that the above variations, may create differences in strain distribution and thus dissimilar biomechanical behaviors of these two nails. The main hypothesis of our biomechanical study is that the InterTan nail would provide higher stiffness and load to failure and less varus collapse in unstable intertrochanteric fractures (AO/OTA A2). The transmission of forces as measured by cortical surface-strain distribution in the proximal femur will be evaluated using digital image correlation (DIC) and classic strain gauges.

#### Preparation of specimens

Eight synthetic composite osteoporotic femurs of medium size (model: 3503; SawBones Worldwide, WA, USA) with 10 PCF low-density cancellous, thin-walled low-density cortical shell and 16 mm hollow canal, would be randomly assigned to two groups (*n* = 4 in each group) to receive either a classic Gamma3 or an IT nail. Two additional specimens will be kept intact and will be served as reference for system calibration and material properties validation. The use of sawbone models with validated mechanical properties [34–36] was preferred instead of cadaveric bones to eliminate size, geometry and mechanical variability between specimens thus increasing stanchness of our numerical analysis due to the availability of the finite element 3D digital file with coded material properties of our specimen (Femur, Finite Element Model of #3503, SawBones Worldwide, WA, USA).

The instrumentation of Gamma3 and IT will be applied in a standard manner, according to the manufacturer’s manual, first on the intact sawbones (prior to fracture creation) under image intensifier using antero-posterior and lateral imaging to ensure proper implant position and a tip-to-apex distance (TAD) < 20 mm (Fig. 1a–c).

**Fig. 1 Fig1:**
[figure not shown]
**a** The instrumentation of Gamma3 has been applied in a standard manner, according to the manufacturer’s manual in an osteoporotic Sawbone model, first on the intact sawbones; **b**–**d** Fluoroscopic images of Gamma3 in the intact and fractured Sawbone; **c**–**e** Fluoroscopic images of InterTan in the intact and fractured Sawbone

The instrumentation will be removed and the fractures would be created using an electric saw and a custom-made cutting guide. For the creation of an unstable intertrochanteric fracture (AO/OTA 31A2.2) the fracture line will be at an angle of 47° to the horizontal level running from the lesser trochanter followed by removal of an additional wedge of bone, containing the lesser trochanter. The sawbones will be re-instrumented and prepared for biomechanical testing (Fig. 1d, e).

The natural inclination of the femur at the single-leg stance, which is 11° of abduction in the frontal plane and neutral on the sagittal plane will be ensured using the surface of the posterior condyle as reference point [37] (Fig. 2a). The femurs will then be fixed distally at the supracondylar level to a custom resin mold (Smooth-Cast 300 Series) properly reinforced with an orthogonal steel plate (Fig. 2b). Standard strain gauges (model C2A-06-125LW-350, 350Ω ± 0.6%, − 50° up to + 80 °C) will be applied at the medial and lateral side of the specimen 2 cm below the fracture line as well as 2 cm below the distal interlocking screw (Fig. 2c). Finally, a thin layer of white paint with black speckles (Fig. 2d) will be applied at the proximal end of the femur to measure the transmission of forces, in the cortical surface-strain distribution using digital image correlation (DIC) (Fig. 2e).

**Fig. 2 Fig2:**
[figure not shown]
**a** position of the composite femur at 11° of abduction in the frontal plane and neutral on the sagittal plane; **b** Fixation of the specimen distally at the supracondylar level to a custom resin mold (Smooth-Cast 300 Series); **c** Standard strain gauges will be applied at the medial and lateral side of the specimen 2 cm below the fracture line as well as 2 cm below the distal interlocking screw; **d** A thin layer of white paint with black speckles will be applied at the proximal end of the femur to measure the transmission of forces, in the cortical surface-strain distribution using DIC; **e** and **f** the biomechanical testing machine and the mode of cycling loading

#### Loading scheme

Once the implants were settled well and distal ends were embedded, the two groups of model bones were fixed on the biomechanical test machine (MTS 647, hydraulic wedge grip) (Fig. 2f). Initially, all specimens will be subjected to an axial pressure of 100–200 N for 10 cycles with a loading rate of 1 Hz to eliminate creeping effect.

Axial cycling load compression will be applied to simulate the stress experienced by a patient with 70 kg body weight at 4–6 weeks postoperatively [38, 39]. Firstly, the axial compression test is carried out under cyclic loading, with an initial load of 400 N, incremental load of 100 N, and maximum load set to 1400 N, divided into 10 subgroups; each subgroup will be conducted in a cycle of 10,000 times, respectively, with a loading rate of 1 Hz. After the cyclic test, the average fracture gap movements will be recorded. A torsional test will follow with the following parameters: Starting from 0°, the maximum torsion angle will be set to 3° with a loading rate of 0.1°/s. Torque at the angle of 1°, 2°, 3° will be recorded, respectively. Finally, an axial compression failure test will be performed with a loading rate of 4.6 mm/s continuously, until fatigue failure; the latter is defined as fracture gap > 20 mm, nail cutting‐out or breakage and fracture line found near the distal locking screw.

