#### Statistical analysis

The SPSS 19.0 statistical software package will produce the statistical analysis of the study. With the aid of Shapiro–Wilk test, the normal deviation of cycles to failure, failure load and axial construct stiffness in each group will be monitored. To screen the fluctuation in the parameters of interest, the Levene test will be utilized. Any major difference between the two implants will be registered with paired-samples *t* test, while we set a *p* = 0.05 as level of significance.

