**Fig. 3 Fig3:**
[figure not shown]
Several FEA models will be created with the aim to study different scenarios of reduction (in varus or valgus) as well as inappropriate lag screw positions

As has been proposed in a similar study [40], the developed geometries will be meshed using tetrahedral elements with an optimal element size of 3 mm as this leads to acceptable results regarding accuracy, without significantly increasing the computational cost. Appropriate linear elastic, isotropic and homogeneous material properties will be assigned to the several parts of the FE model, based on the data provided by the manufacturers. The longitudinal Young’s modulus for the cortical bone (82 pcf fiber filled epoxy) is E_cortical_ = 5.2 GPa, and for the cancellous bone (10 pcf solid foam) E_cancellous_ = 58 MPa, while for the Gamma3 and IT the titanium alloy the Young’s modulus is E_material_ = 116 GPa. For the modeling of the distal femoral fixation during the experiments, fully fixed boundary conditions will be applied on the FE models surface nodes situated at the lower 130 mm of the femur model. A constant vertical force of 1000 N will be applied on the top of the femoral head; as a linear-elastic FE analysis will be considered, the calculated results will be derived for other load values using linear interpolation or extrapolation. Linear regression modeling will be utilized in order to associate a set of independent variables or predictors (implant type, lag screw(s) positioning and reduction angle) with any measurement outcome, also referred to as the dependent variable or target, separately. For each model, the beta estimates and the *p* values will be returned, among others. Statistical significance was taken when *p* < 0.05.

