### Limitations

Our study has several limitations. Firstly, the surgery will be performed by several orthopedic surgeons of our department that have different surgical experience, but they all were trained at the same hospital and the reduction will be closed monitored to be as anatomical as possible. Second, the assessment of fracture healing, cut-out, varus displacement and other complications will be measured with digitalized radiographs that can be misinterpreted by wrong patient positioning and intraobserver variability. Third, there are many factors contributing to fracture healing and regain of functional status that are mostly patient depended, especially in these fragile population of > 70 years old. The main weaknesses of the biomechanical study are its static nature and uniplanar loading configuration. Mechanical failure is a dynamic event in clinical practice, and rotational displacement is equally important to frontal plane displacement postoperatively. However, the current study will test the initial loading characteristics of various lag screw(s) configurations at subcritical stress levels and can serve both as a guide at events at early postoperative ambulation status and as a reference for future dynamic studies with more complex loading characteristics.

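### Cycles to failure and failure load cannot both be observed across the eight bench femurs, so the planned t tests are either empty or restricted to survivors

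*Protocol article*

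**What the plan says.** Preparation of specimens assigns eight synthetic femurs at random, four to each nail. Two more stay intact for calibration, so none is set aside for a separate torsion or failure test.

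Loading scheme fixes one order for every implanted femur:

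1. Ten settling cycles at 100–200 N.
2. Stepped cyclic compression: "initial load of 400 N, incremental load of 100 N, and maximum load set to 1400 N, divided into 10 subgroups", where "each subgroup will be conducted in a cycle of 10,000 times, respectively, with a loading rate of 1 Hz".
3. Torsion to 3°: "After the cyclic test, the average fracture gap movements will be recorded. A torsional test will follow with the following parameters".
4. A ramp: "Finally, an axial compression failure test will be performed with a loading rate of 4.6 mm/s continuously, until fatigue failure". The failure criteria (gap size, cut-out, breakage, a fracture line near the distal screw) are attached to this step alone.

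The bench Statistical analysis section says that "the normal deviation of cycles to failure, failure load and axial construct stiffness in each group will be monitored", then compares the nails with a t test at 0.05. The Introduction gives the bench aim as a comparison "in relation to axial stiffness, torsional stiffness, and failure load". The Discussion states the hypothesis on stiffness and load to failure as holding after cyclic loading. Limitations instead calls the bench study static and says that "the current study will test the initial loading characteristics of various lag screw(s) configurations at subcritical stress levels".

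**The concern.** The two failure endpoints belong to different outcomes of the same sequence. Cycles to failure is observed only when a femur fails in the cyclic phase. The torsion reading and the ramp load are obtained only when it does not. The plan analyses both endpoints as if every femur had a value for each.

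It also labels the end of a monotonic ramp fatigue failure and gives no criterion for failure during cycling. A reader therefore cannot tell which event counts as failure for which endpoint.

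Failure load is a stated aim and part of the main bench hypothesis. If the weaker constructs drop out during cycling, the remaining comparison of torsion and failure load is conditional on survival. If none drops out, one of the three listed endpoints has no observed values.

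**Working it through.** **Inputs from the document.** Start 400 N, step 100 N, maximum 1400 N, 10 subgroups, 10,000 cycles per subgroup at 1 Hz (Loading scheme); 4 femurs per nail (Preparation of specimens); significance level 0.05 (bench Statistical analysis). Two-sided testing is assumed because sidedness is not stated.

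**The plan's own count.** Increments: (1400 − 400)/100 = 10. Load levels including both ends: 10 + 1 = 11. The stated 10 is reproduced only if one of the two end loads is not cycled.

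| Reading | Cycles | Time at 1 Hz |
|---|---|---|
| 10 subgroups | 10 × 10,000 = 100,000 | 100,000/3600 = 27.8 h |
| 11 levels | 11 × 10,000 = 110,000 | 110,000/3600 = 30.6 h |

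The censoring point for cycles to failure is therefore 100,000 or 110,000.

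**What each femur can supply.**

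| Course of the femur | Cycles to failure | Torsion | Ramp failure load |
|---|---|---|---|
| Fails in cycling | observed | none | none |
| Survives cycling | censored | observed | observed |

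If all eight survive, all eight cycle counts equal the censoring point and a t test has nothing to compare. Each femur that fails in cycling removes 1/4 = 25% of its arm from torsion and ramp load.

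**How likely a loss is.** The documents give no failure rate, so the probability q that a femur fails in cycling is assumed, equal and independent across femurs. P(at least one of eight) = 1 − (1 − q)^8.

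| q | 0.05 | 0.10 | 0.25 | 0.50 |
|---|---|---|---|---|
| P | 34% | 57% | 90% | 99.6% |

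**What a loss costs in precision.** Independent two-sample t test, noncentral t, two-sided 0.05:

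| Femurs | Difference detectable with 80% power | Power at 2.38 SD |
|---|---|---|
| 4 v 4 | 2.38 SD | 80% |
| 4 v 3 | 2.68 SD | 70% |
| 3 v 3 | 3.07 SD | 60% |

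**What a loss does to the estimate (illustration).** Assume normal strengths with a true difference of 1 SD, and let every femur below a common threshold fail in cycling. If 16% of the weaker and 2% of the stronger arm are lost, the difference among survivors is 0.77 SD. With 50% and 16% lost it is 0.49 SD. This assumes that resistance to cycling and ramp strength are the same quantity; a weaker link would give less shrinkage.

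**Limitations against the rest of the article.** Static conflicts with a cyclic phase of about 28–31 hours. Subcritical conflicts with a test run to failure.

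**The case against.** **Measuring after cycling is the declared target.** A reader might infer that wear carried over from cycling biases torsion and failure load. The documents do not support that. The Discussion states the hypothesis after cyclic loading, Loading scheme says that the load represents a patient some weeks after surgery, and both nails get the same sequence. If one nail degrades more, that is part of the effect sought. This objection stands.

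**The finite element model.** A reader might also infer from "A constant vertical force of 1000 N will be applied on the top of the femoral head" that validation must wait until the bench reaches 1000 N, after 50,000–60,000 cycles. That does not follow. The same section lets the linear results be scaled to other loads, so strains from early cycles or the settling load would serve. The article does not say when strains or axial stiffness are read. This objection stands too.

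**No femur is shown to fail.** Nothing in the article shows a failure at or below 1400 N, so the survivor problem is conditional. If none fails, torsion and failure load are complete. But cycles to failure then has no observed value, so the plan does not work as written in that case either.

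**Failure load may not mean ramp load.** It would be too absolute to say that no femur can have both a cycle count and a failure load: one that breaks in cycling has a step load at failure. But a cyclic step load and a monotonic ramp load are different measurements, and the article does not say that they may be pooled. Survivors still have censored counts, and early failures still lack torsion.

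**Handling rules may sit in a fuller plan.** For detail this is fair. Here, however, the sequence, the two endpoints and the t test are all stated, and no handling rule can give all eight femurs observed values for both.

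**The word initial.** It may mean early postoperative loading, since the same sentence refers to early walking. That reading is plausible; static and subcritical still need correcting.

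**Conclusion.** The point holds for the failure endpoints. The stated sequence and the stated analysis do not fit together: with no failures in cycling, cycles to failure is censored for all eight femurs; with any failure, torsion and ramp failure load are compared among survivors only, at a cost of 25% of an arm per femur. Under assumed failure probabilities of 5% to 25% per femur, the chance of at least one such loss is 34% to 90%.

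That the weaker nail is flattered is a tendency, not a demonstrated bias. It needs the weaker nail to fail more often in cycling, and the failing femurs to be those that would have had low ramp loads. The Limitations wording is a separate, editorial inconsistency.

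The issue is confined to the bench substudy and touches no analysis of the randomised trial. It is worth fixing before testing starts, because specimens tested to failure cannot be retested.

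**What to change.** 1. **Define failure once.** Apply the failure criteria to the cyclic phase as well as the ramp, do not call the end of the ramp fatigue failure, and state whether 10 or 11 load levels are run.
2. **Use one ordered failure endpoint for all eight femurs.** Rank femurs that fail in cycling by stage and cycle reached, below every survivor. Rank survivors by ramp failure load. Analyse with an exact rank test for two independent groups.
3. **Say what is measured when.** State that torsion and failure load are post-cycling properties, in line with the Discussion, and give the time of the axial stiffness reading. Report post-cycling torsion with the number of femurs contributing.
4. **Correct Limitations.** Remove static and subcritical, and clarify initial.
5. **Optional supplement.** Before cycling, take an axial reading with strain gauge and image-correlation capture at the settling load, and a short torsion run. This gives data on all eight femurs and an early reference for the finite element model. It should not replace the post-cycling endpoints, which the hypothesis concerns.

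**Cost.** Items 1–4 need a few sentences and no extra specimens. The rank test is coarse: with 4 v 4 there are 70 possible allocations, so complete separation gives p = 2/70 = 0.029 and the next result 4/70 = 0.057. Only complete separation reaches 0.05. The optional torsion run takes 3/0.1 = 30 s per femur if taken to the full 3°. It adds a small load before cycling, the same in both groups.
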